### Nested qualitative study

#### Aims

The aim of the qualitative component of the feasibility assessment are to explore the following:Patient views on the acceptability and suitability of the physiotherapy treatment received.Patient views on study processes, e.g. experience of being recruited into the trial, reasons for declining participation, acceptability of study information and measurement of outcomes.Clinician views on the acceptability and feasibility of delivering the optimised physiotherapy treatment package in an NHS setting.

#### Recruitment and sampling

Approximately, 16 participants from the pilot and feasibility RCT, including some that declined to take part, will be purposively sampled and interviewed by the chief investigator. Patients will be selected from both treatment arms and also from those that were eligible but did not consent to the trial but were willing to be interviewed. A varied sample will be obtained, in relation to characteristics such as trial site, age, gender, baseline tennis elbow pain and function and adherence to treatment (including patients that withdrew, if applicable).

Information relating to the qualitative interviews is included in the initial patient information sheet, and an option to give consent to further contact for the interviews is included in the consent form. Two months following initial assessment and randomisation, patients who have consented to further contact will be sent an invitation letter and patient information sheet before receiving a follow-up telephone call or email from the CI to confirm interest and arrange a suitable interview date. Patients will be able to decline participation in the interviews yet continue to be involved in the pilot and feasibility trial.

Similarly, approximately 9 physiotherapists involved with delivering the optimised physiotherapy intervention will be recruited from different sites. All physiotherapists on the trial delegation log will be approached with written information regarding the qualitative interviews, and from those that consent a broad sample of age, gender, clinical experience and site location will be sampled.

#### Qualitative data collection

Semi-structured interviews will be conducted with patient participants at least 2 months following randomisation either face to face, via video-conference or via telephone, depending on participant preferences. The interviews will be informed by topic guides developed in relation to the prespecified aims but also with PPIE input.

Physiotherapists will be interviewed following the end of their involvement with patients in the pilot and feasibility trial to allow time to reflect on their experiences of delivering the intervention to a number of patients in the RCT.

Consent will be obtained at the start of the interview, either in writing if the interview is face to face or audio recorded if the interview is over the telephone or video-conference, and checked again at the end. Interviews will be audio recorded and transcribed verbatim.

Participants that are interviewed will receive a £20 voucher for their time, and travel expenses will be reimbursed if the interviews are held in the physiotherapy department.

#### Qualitative data analysis

Anonymised interview transcripts will be analysed using thematic analysis, applying the COM-B model of behaviour change [22], to assess acceptability to recruitment and intervention delivery across the dataset in relation to views of patients and physiotherapists [23, 24]. Analysis will begin with the first data collection and continue until key theme data saturation is reached [25]. Using the theoretical framework of the COM-B model [21] allows us to more fully explore the aspects of patient and physiotherapist behaviour change [22]. The COM-B offers a way of understanding behaviour around three key determinants: *capability* — the psychological or physical ability to enact the behaviour, *opportunity* — the physical and social environment that enables the behaviour and *motivation* — the reflective and automatic mechanisms that activate or inhibit behaviour. The COM-B model is an extension of the earlier Theoretical Domains Framework (TDF) [26], which synthesises 112 psychological constructs determining behaviour change into 14 domains, which can be used to identify barriers and facilitators to behaviour change in the context of clinical interventions. The COM-B integrates these 14 domains within its three core components. The model has been successfully used in several recent studies exploring the feasibility of delivering complex interventions [27–29].

The following process will be adopted within and across both sets of participants, concurrent with iterative data collection to incorporate exploration/checking emerging themes and their implications in subsequent interviews:Analysis will comprise distinct stages beginning with each case/transcript before moving to a cross-case comparison:*Level 1*: Read through individual transcripts/make preliminary notes.*Level 2*: Identify segments of meaning; apply initial codes.*Level 3*: Group initial labels to overarching within-case codes of meaning*Level 4*: Cross-case comparisons: looking for similarities, differences and inconsistencies, resulting in meta-codes spanning all cases/transcripts.*Level 5*: Cross data sets comparison, as above*Level 6*: Situating findings within the context of the physiotherapy interventions delivered and comparing responses between patients in the intervention group and the control group*Level 7*: Explore implications for intervention refinement for testing in a future main trial from the perspective of both the patient and the physiotherapist.2.Analytic memos will be kept as the coding proceeds and will provide an audit trail to explain how codes develop and change.3.A codebook consisting of a structured compendium of codes will be developed, including a description of how the codes are related to each other. It is anticipated that the codebook for physiotherapists and patients will differ in some respects.4.Full coding team will analyse and agree codes and theoretical constructs at levels 3, 5, 6, and 7 and then map the themes to the three core components of capability, opportunity and motivation from the COM-B model.5.The outcome will contribute to the assessment of future main trial feasibility and also provide valuable feedback that will be used to refine the intervention, supporting documentation and study processes.

### Data management

Data will be collected using a mix of paper and electronic methods. Where possible, a patient ID number will be used rather than identifiable information. Data from paper forms will be transcribed into an electronic database in Microsoft Excel stored on secure servers provided by the sponsor. Paper hard copies will be stored at the CTU and in the relevant Investigator Site Files. Study documentation will be stored securely (i.e. cupboards, shelves or filing cabinets with restricted access, e.g. within a locked office) to maintain participant confidentiality and study data integrity.

Electronic data captured at trial sites will be sent to the research team by secure NHS email. Online outcome data collection will be managed by Amplitude Clinical in ISO27001 Tier 3+ data centres approved for use by the NHS. Amplitude Clinical will not own the data — ownership is retained by the sponsor.

In order for patients to use the Squegg device, they will need to install the Squegg app on an Apple or Android smartphone/tablet. They are required to create an account within the app or log in using a Facebook or Google account. For data privacy reasons, participants will be recommended to use an email address rather than Facebook to create a user account; however, this is their own personal choice. No data will be shared between Squegg and the research team. Patients will use the device to measure grip strength and report the numerical values on the OPTimisE Follow-up Questionnaire.

Qualitative data will be organised and managed using NVivo software. Audio recordings and transcriptions will be stored on secure servers provided by the sponsor. An NHS-approved transcription service will be used that complies with data security regulations.

### Statistical methods

Descriptive statistics will be presented to summarise the distribution of baseline variables across each of the randomisation groups. The continuous baseline variables (e.g. age) will be reported with means, and 95% confidence intervals (95% CI), if shown to be normally distributed, using a combined skewness and kurtosis test, otherwise will be reported with medians and interquartile ranges (IQR). The categorical variables (e.g. gender) will be reported with frequencies and percentages.

A Consolidated Standards of Reporting Trials (CONSORT) flow diagram will be produced, showing the numbers and frequency of patients/participants: assessed for eligibility, reasons for ineligibility, screened as eligible, excluded before consent (and the frequency of each reason for exclusion), consented, excluded before randomisation (and the frequency of each reason for exclusion), randomised, allocated to each randomisation group, which received each allocated intervention, which did not receive each allocated intervention, lost to follow-up (and the frequency of each reason for loss to follow-up) for each analysis group, analysed for each analysis group and not analysed (and the frequency of each reason for not being analysed) for each analysis group.

Quantitative data analysis will be descriptive. This feasibility study aims to provide estimates of the consent, intervention fidelity, follow-up and outcome measure completion rates to inform a future main trial. By including 50 participants, we will be able to estimate a consent rate of 25% with a 95% confidence interval of (19%, 31%), an intervention fidelity of 60% with a 95% confidence interval of (46%, 74%) and a follow-up rate and outcome measure completion rate of 70% with a 95% confidence interval of (57%, 83%).Consent rate — measured as a percentage of eligible patients approached to participateIntervention fidelity in the intervention group — measured using CRF data. Fidelity to the intervention will be defined by delivery of at least 6 of the 12 prescribed advice/education topics, evidence of exercise prescription and progression in line with the protocol and provision of an elbow clasp splint. Results will be expressed as a percentage of the patients in the intervention group who received treatment assessed as being faithful to the protocol.Follow-up rate in the intervention group — the actual number of visits (excluding the baseline visit) divided by the maximum number of possible visitsOutcome measure completion rate at 6 months — measured as a percentage of outcome measures completed across both the intervention and usual care groups

If any of the above feasibility outcomes are rated red (do not proceed) as per Table 2, then a future main trial will not be feasible. If any outcomes are rated amber (proceed with changes), but without any red, then a future main trial may be feasible with changes to the protocol. If all outcomes are rated green (proceed), then a main trial is feasible.

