### Sample size

The pilot and feasibility RCT will recruit up to 50 participants or for a maximum of 12 months across three sites. These limits were a condition stipulated by the funder. The nested qualitative study will recruit until data saturation, estimated as up to 25 participants (approximately 16 patients and 9 treating physiotherapists).

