### Assignment of interventions

#### Allocation sequence generation

Patients will be randomised in a 1:1 allocation (in mixed blocks) stratified by site using an online randomisation service provided by the CTU. Mixed blocks are required to reduce the predictability of the randomisation allocations.

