**Table 3 Tab3:**
[figure not shown]
Schedule of events

*t*_0_ additional research clinic appointment *t*_1_ first physiotherapy treatment clinic appointment

Mean values and confidence intervals of the secondary outcomes (see Table 4) will be calculated if the data are normally distributed (this will be assessed using a combined test of skewness and kurtosis). If the data are not normally distributed, medians and interquartile ranges will be reported. The responsiveness of the different outcome measures will be compared, by calculating the treatment effect in the intervention group.

**Table 4 Tab4:** Outcome measures and time-points

Outcome measure	Baseline	6 weeks	3 months	6 months
Numerical rating scale of pain on gripping	X	X	X	X
Patient-rated tennis elbow evaluation (PRTEE) [15]	X	X	X	X
Tampa scale of kinesiophobia (TSK-11) [16]	X	X	X	X
Pain self-efficacy questionnaire (PSEQ) [17]	X	X	X	X
EQ 5D5L [18]	X	X	X	X
Pain-free grip strength (lbs)	OPTimisE group X	OPTimisE group X	OPTimisE group X	OPTimisE group X
	Usual care group X	Usual care group	Usual care group	Usual care group X
Maximum grip strength (lbs)	OPTimisE group X	OPTimisE group X	OPTimisE group X	OPTimisE group X
	Usual care group X	Usual care group	Usual care group	Usual care group X
Global perceived effect (GPE-11) [19]		X	X	X
Exercise adherence rating scale (EARS) [20]		X	X	X

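### A normality test on at most about 25 patients per arm chooses between mean with 95% CI and median with IQR, and neither branch names an SD

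*Protocol article*

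**What the plan says.** The Statistical methods section of the Protocol article opens with its aim for the baseline table: "Descriptive statistics will be presented to summarise the distribution of baseline variables across each of the randomisation groups". For continuous variables it then fixes the format by a test. They "will be reported with means, and 95% confidence intervals (95% CI), if shown to be normally distributed, using a combined skewness and kurtosis test"; failing that, median and IQR are given.

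The paragraph between Tables 3 and 4 applies the same rule to the outcomes: "Mean values and confidence intervals of the secondary outcomes (see Table 4) will be calculated if the data are normally distributed", judged by the same kind of test. The other branch reads: "If the data are not normally distributed, medians and interquartile ranges will be reported".

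Neither branch names a standard deviation, and the article mentions none elsewhere. It does not give the significance level of the test. It also does not say whether the test is run per arm, per visit or on pooled data. On size, the trial will "recruit up to 50 participants or for a maximum of 12 months across three sites" (Sample size), and "Patients will be randomised in a 1:1 allocation (in mixed blocks) stratified by site" (Allocation sequence generation).

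**The concern.** There are three difficulties with the rule.

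- **It does not fit its purpose at baseline.** A 95% CI describes how precisely a mean is known and narrows as n grows. It does not show how patients vary, which is what a summary of a distribution is for.
- **The selector is weak.** With so few patients, a skewness-kurtosis test misses much real skewness and still rejects some normal samples. The format of a table cell then depends partly on chance.
- **The rejecting branch drops both mean and SD.** Responsiveness of the outcome measures is a listed secondary outcome, to be compared through the treatment effect in the intervention group. The Table 4 measures are in different units, so comparing them needs one common statistic and a measure of spread. The study also exists to prepare a fully powered RCT, and powering such a trial on a continuous outcome needs an SD.

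**Working it through.** **Plan's own figures.** The article attaches no number to this rule, so there is none to reproduce. One stated interval supplies an input: a 70% completion rate with 50 patients gives 0.70 ± 1.96 × √(0.70 × 0.30/50) = 57.3% to 82.7%, which matches the stated 57% to 83%.

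**Inputs from the article.** Up to 50 patients at 1:1 gives at most 50/2 = 25 per arm. With 70% completion, 25 × 0.70 = 17.5, or about 18 per arm.

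**Assumptions.** The test is taken as the D'Agostino-Pearson combined test at 5%. The article gives no distribution for any scale, so a range of shapes was simulated, 20,000 samples per case. A gamma distribution with shape k has skewness 2/√k, so k = 16 gives 0.5 and k = 4 gives 1. Two bounded shapes were added because the rating scales are bounded: a rounded normal (mean 3, SD 2.5) cut to 0–10, and a beta(1.2, 3).

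**Step 1: how often the test rejects (r).**

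| Shape | n = 18 | n = 25 | n = 50 (arms pooled) |
|---|---|---|---|
| Normal | 5.8% | 5.7% | 5.6% |
| Gamma, skewness 0.5 | 10.6% | 12.6% | 20.8% |
| Gamma, skewness 1 | 23.5% | 30.9% | 54.5% |
| Lognormal, sigma 0.5 | 40.2% | 52.4% | 82.6% |
| 0–10 scale with floor | 7.0% | 10.0% | 18.9% |
| Beta(1.2, 3) | 14.0% | 17.4% | 35.5% |

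At n = 25 the test misses 100 − 30.9 = about 69% of samples with skewness 1. Pooling the arms does not make the choice stable: at n = 50 and skewness 1 it is close to a coin toss, so one measure can still change format from visit to visit.

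**Step 2: arms in different formats, only if each arm is tested separately.** With independent arms of the same shape, the chance is 2r(1 − r). At n = 25:

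- normal: 2 × 0.057 × 0.943 = 10.8%
- skewness 0.5: 2 × 0.126 × 0.874 = 22.0%
- skewness 1: 2 × 0.309 × 0.691 = 42.7%
- 0–10 scale with floor: 2 × 0.100 × 0.900 = 18.0%
- beta: 2 × 0.174 × 0.826 = 28.7%

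Table 4 has 64 arm-by-visit cells: 5 measures × 4 times × 2 arms = 40; two grip measures × (4 + 2) = 12; GPE and EARS, 2 × 3 × 2 = 12. If all were normal and each were tested, 64 × 0.05 = 3.2 to 64 × 0.06 = 3.8 would switch to median and IQR by chance.

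**Step 3: what can be recovered.**

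- *Mean/CI branch:* SD = half-width × √n / t. At n = 25 this is half-width × 5/2.064 = 2.42 × half-width; at n = 18, 2.01 × half-width. The SD is recoverable if n is shown.
- *Median/IQR branch:* the SD can only be approximated, for example as IQR/1.349. Relative to the true SD this was 0.96 for gamma with skewness 1, 0.84 for the lognormal and 1.09 for the beta. Sample size goes with SD², so a main-trial N would be off by a factor of 0.84² = 0.71 to 1.09² = 1.19.

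**The case against.** The strongest reply has four parts.

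1. **Unit of testing.** The wording makes the variable, or simply the data, the subject of the test. One decision per variable is a natural reading, and under it the arms always share a format. This stands. A reader might infer that arms will be summarised differently, but the article does not say so, and Step 2 holds only for separate testing by arm. For grip strength at 6 weeks and 3 months there is no second arm to compare. Single decisions do not remove differences between measures, and one decision per visit still allows differences between visits.

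2. **Availability of SDs.** A reader might infer that the SDs for the main trial will be unavailable. That goes too far: the mean branch allows back-calculation, and the sponsor holds the individual data, so an SD can be computed at any time. What stands is narrower: where the test rejects, the planned report gives neither mean nor SD.

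3. **Objectives.** Estimating outcome SDs is not listed. The stated estimates are consent, fidelity, follow-up and completion rates, and none of the red/amber/green ratings uses this rule. This stands and limits the importance. The sentence on responsiveness is also not itself conditional on the normality test, so that analysis is hampered by the surrounding summaries rather than prevented.

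4. **Level of detail.** Table layouts may be left to an analysis plan, and choosing the summary by a normality test is conventional in descriptive work. However, the point here is a rule that the article states, not a detail it leaves out.

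**Conclusion.** The concern holds as a reporting point of minor to moderate importance. The stated rule gives no direct measure of spread when the test passes, and neither mean nor SD when it rejects. The choice rests on a test that, at 25 per arm, rejects about 6% of normal samples and about 31% at skewness 1. Formats may therefore change between visits and measures. Arms may differ in format about 11% (normal) to 43% (skewness 1) of the time, but only if each arm is tested separately.

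These rates rest on an assumed 5% level and assumed shapes; the bounded shapes give lower rejection rates at n = 25 (10% and 17%) than skewness 1 does. The analysis is descriptive, so no error rate is distorted, and the decision on whether a main trial is feasible is untouched. The practical loss is to the responsiveness comparison and to planning the fully powered RCT.

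**What to change.** Delete the normality test from both places in Statistical methods. For every continuous variable, by arm and time-point, report n, mean, SD, median and IQR. Keep confidence intervals for follow-up estimates and drop them from the baseline description. No test then chooses the format, and every cell has an SD.

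The cost is two reworded sentences and extra table columns; no new data are needed. The pooled SD and the baseline-to-6-month correlation of candidate main-trial outcomes would be useful for planning, but they are optional additions rather than corrections.

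### The 95% confidence intervals for intervention fidelity and follow-up rate are worked out on all 50 participants, although both outcomes are defined in the intervention group only (about 25 patients)

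*Protocol article*

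**What the plan says.** The Sample size section sets the ceiling: "The pilot and feasibility RCT will recruit up to 50 participants or for a maximum of 12 months across three sites". It adds that the funder imposed these limits. Allocation sequence generation sets the split: "Patients will be randomised in a 1:1 allocation (in mixed blocks) stratified by site".

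Statistical methods gives the expected precision for the four primary feasibility outcomes. It begins "By including 50 participants, we will be able to estimate a consent rate of 25% with a 95% confidence interval of (19%, 31"%), continues with "an intervention fidelity of 60% with a 95% confidence interval of (46%, 74%) and a follow-up rate and outcome measure completion rate of 70"%, and gives the last two the limits 57% and 83%. The 70% interval thus serves two outcomes at once.

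The same section then defines the outcomes:

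- **Fidelity** is counted per patient in one arm: "Results will be expressed as a percentage of the patients in the intervention group who received treatment assessed as being faithful to the protocol".
- **Follow-up** is headed "Follow-up rate in the intervention group". It is the visits made after baseline as a share of the visits that could have been made.
- **Outcome completion at 6 months** is the percentage of outcome measures completed, taken over both arms.

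The Outcomes section also restricts fidelity and follow-up to the intervention group.

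**The concern.** The introductory sentence attributes all the stated precision to 50 participants, but two of the four outcomes can draw on only about half of them. The usual care arm contributes nothing to fidelity or follow-up as defined. An interval calculated on both arms therefore describes data that these outcomes will not have.

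The study says that its quantitative aim is to estimate these rates for a future main trial, and these intervals are the only statement of how well it will do so. The outcomes also feed a red/amber/green rule under which one red rating makes a main trial not feasible. A reader judging how firmly the pilot can support that decision would take fidelity to be known to within about 14 points either way, when the design gives about 19.

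**Working it through.** **Inputs from the protocol article**

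- Total randomised: at most 50 (Sample size; Statistical methods).
- Allocation 1:1 (Allocation sequence generation), so the intervention group is about 50/2 = 25.
- Anticipated rates: consent 25%, fidelity 60%, follow-up 70%, completion 70% (Statistical methods).

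**Formula.** Wald interval: p ± 1.96 × √(p(1 − p)/n).

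**Step 1: reproduce the stated figures**

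- Fidelity, n = 50: 1.96 × √(0.6 × 0.4/50) = 13.6 points, giving (46.4%, 73.6%). This rounds to the stated (46%, 74%).
- Follow-up and completion, n = 50: 1.96 × √(0.7 × 0.3/50) = 12.7 points, giving (57.3%, 82.7%). This rounds to the stated (57%, 83%).
- Consent: 50 consenting at 25% implies 50/0.25 = 200 approached. Then 1.96 × √(0.25 × 0.75/200) = 6.0 points, giving (19%, 31%) as stated.

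The consent interval therefore does fit that outcome's own denominator.

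**Step 2: could another sample size or method explain the stated limits?** With the Wald formula, the whole numbers that reproduce both rounded limits are 44 to 50 for fidelity and 45 to 51 for the 70% interval. At n = 25 the usual alternatives do not reproduce them either:

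| Method, n = 25 | 60% | 70% |
|---|---|---|
| Wilson | (40.7%, 76.6%) | (50.4%, 84.3%) |
| Clopper-Pearson | (38.7%, 78.9%) | (48.5%, 86.5%) |
| Continuity-corrected Wald | (38.8%, 81.2%) | (50.0%, 90.0%) |

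**Step 3: fidelity on its own denominator.** With n = 25: 1.96 × √(0.6 × 0.4/25) = 19.2 points, giving (40.8%, 79.2%), or about (41%, 79%). The width ratio is √(50/25) = 1.41, so the interval is 41% wider. As a share of the correct width, the stated one is too narrow by 1 − 1/1.41 = 29%.

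**Step 4: follow-up.** If the patient is the unit, n = 25 gives 1.96 × √(0.7 × 0.3/25) = 18.0 points, or (52.0%, 88.0%).

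The outcome is, however, a ratio of visits clustered within patients. With m possible visits for each patient and within-patient correlation ICC, the effective sample size is 25m/(1 + (m − 1) × ICC). The document gives neither m nor ICC, so the values below are assumptions:

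| m | ICC | Effective n | Half-width (points) |
|---|---|---|---|
| any | 1 | 25 | 18.0 |
| 2 | 0.5 | 33.3 | 15.6 |
| 3 | 0.3 | 46.9 | 13.1 |
| 4 | 0.3 | 52.6 | 12.4 |
| 6 | 0.3 | 60.0 | 11.6 |
| 6 | 0 | 150 | 7.3 |

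The stated half-width of 12.7 points lies inside this range. It is matched exactly only for particular pairs, such as m = 3 with ICC 0.25: 75/(1 + 2 × 0.25) = 50.

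**Step 5: completion.** This outcome covers both arms, so n = 50 is the right number of participants, and (57%, 83%) stands as a participant-level figure.

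**Step 6: shortfall.** Fifty is a maximum. If 40 were recruited (20 per arm), the patient-level half-widths would be 1.96 × √(0.24/20) = 21.5 points for fidelity and 1.96 × √(0.21/20) = 20.1 points for follow-up.

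**The case against.** **Follow-up counts visits, not patients.** This stands. A reader might infer from the sample sizes alone that follow-up precision, like fidelity, is overstated by some 40%. The document does not support that: visit numbers and correlation are not given, and the true width could be larger or smaller than the stated one. What remains is that the stated basis is wrong. It counts usual care patients, and it shares one interval with an outcome measured in both arms. Agreement with a visit-based calculation would be coincidence.

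**Fidelity is described in two ways.** Data collection methods describes a percentage of applicable treatment items delivered, whereas Statistical methods classifies each patient as treated faithfully or not. The (41%, 79%) interval follows from the second description, which appears alongside the stated interval. The first does not rescue n = 50, because it too concerns only the optimised intervention.

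**Completion may not be one observation per participant.** This is fair. It is a percentage of outcome measures, so (57%, 83%) matches the arms but needs a label for its unit.

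**The practical consequence is limited.** This also stands. The funder fixed the ceiling of 50, so these intervals did not set the sample size, and the rating rule in the visible text uses no interval. A reader might infer that the stop/go decision itself is faulty or that the pilot is too small. Neither follows. The Table 2 cut-offs are not legible in the text at hand, so no probability of a wrong rating can be derived from it.

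**Conclusion.** The stated precision is wrong as written for two of the four primary feasibility outcomes, and nothing elsewhere in the article corrects it.

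For fidelity the size of the error is firm: about (41%, 79%) in place of (46%, 74%). This rests on the per-patient definition in Statistical methods, full recruitment of 50, an even split and the same Wald formula.

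For follow-up only the error of basis is established. The interval (52%, 88%) is the wide end of the range, and it assumes the patient as the unit or, equivalently, complete within-patient correlation with equal numbers of possible visits. It should not be read as the proven correct interval.

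The consent interval is sound, and so is the completion interval at participant level. This is an error in a descriptive precision statement. It merits correction but does not unsettle the design, the analysis or the rating rule as far as the text shows.

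**What to change.** In Statistical methods:

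- Restate fidelity as 60%, 95% CI (41%, 79%), on about 25 intervention-group patients, and say that it uses the per-patient definition.
- Separate follow-up from completion. Restate follow-up on the intervention group, with its unit and its assumed number of visits and within-patient correlation. Give 70% (52%, 88%) as the conservative patient-level figure.
- Keep 70% (57%, 83%) for 6-month outcome completion across both arms only, labelled as a participant-level figure.
- Put the denominator beside each rate: about 200 approached for consent, about 25 intervention-group patients for fidelity, about 25 for follow-up (or the number of possible visits), and 50 for completion.

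The cost is a few lines of wording and a less favourable statement of precision. No extra patients and no change of design are needed.

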### Interventions

Patients will be randomly allocated to receive either the optimised physiotherapy treatment package, by physiotherapists specifically trained to deliver this, or usual physiotherapy care delivered by other physiotherapists not trained in the optimised intervention but trained in the RCT procedures.

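### The planning interval for intervention fidelity assumes 50 independent patients, but fidelity is measured in about 25 patients nested within a limited group of physiotherapists, so the stated precision is too favourable

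*Protocol article*

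**What the plan says.** All of the following is in the protocol article.

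- **Precision (Statistical methods).** The intervals are tied to the whole trial: "By including 50 participants, we will be able to estimate a consent rate of 25% with a 95% confidence interval of (19%, 31"%). The same sentence continues with "an intervention fidelity of 60% with a 95% confidence interval of (46%, 74"%).
- **Size and allocation.** Under Sample size: "The pilot and feasibility RCT will recruit up to 50 participants or for a maximum of 12 months across three sites". Under Allocation sequence generation: "Patients will be randomised in a 1:1 allocation (in mixed blocks) stratified by site".
- **Denominator for fidelity (Statistical methods).** "Results will be expressed as a percentage of the patients in the intervention group who received treatment assessed as being faithful to the protocol".
- **What is scored (Statistical methods).** A patient's treatment counts as faithful when enough education topics were covered (6 of 12), exercise was prescribed and progressed as planned, and a brace was supplied.
- **Who delivers it.** Under Interventions, the package is given "by physiotherapists specifically trained to deliver this", and usual care is given by others. For the interviews, Recruitment and sampling says "approximately 9 physiotherapists involved with delivering the optimised physiotherapy intervention will be recruited from different sites", and Qualitative data collection says these staff are to have time "to reflect on their experiences of delivering the intervention to a number of patients in the RCT".
- **Consequence (Statistical methods).** Fidelity is one of four primary outcomes rated red, amber or green. One red rating on any of them rules out a main trial.

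**The concern.** The interval is the only statement of how well the pilot can estimate fidelity. Two features of the design make it too narrow.

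First, it is calculated on both arms, although usual-care patients contribute nothing to this outcome.

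Second, it treats patients as independent. The scored items are largely acts of the physiotherapist, and all required components must be present. A physiotherapist who habitually leaves one out would therefore tend to fail with every patient treated. Results for patients of the same physiotherapist can be expected to be correlated.

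At stake is how firmly the fidelity rating can be read. A pooled 60% is also ambiguous. With nine physiotherapists and equal caseloads, it could mean that all are near 60%, or that seven are near 77% and two are at zero (7 × 77 / 9 ≈ 60). The first points to the package and the second to training, and these lead to different changes before a main trial.

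**Working it through.** **Inputs.** Expected fidelity p = 0.60, total n = 50 and 1:1 allocation come from the article, so the intervention group is 50 / 2 = 25. The number of delivering physiotherapists k and the intra-therapist correlation (ICC) are not given. Nine is the interview target and is used as one scenario. All ICC values are assumptions.

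**1. Reproduce the stated interval.** Wald: p ± 1.96 × √(p(1 − p)/n).
0.60 ± 1.96 × √(0.24/50) = 0.60 ± 0.136, or (46.4%, 73.6%), which rounds to the stated pair. At n = 50, Wilson gives (46.2%, 72.4%) and Clopper–Pearson (45.2%, 73.6%); neither rounds to it.

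The consent interval in the same sentence reproduces with n = 50 / 0.25 = 200 patients approached: 0.25 ± 1.96 × √(0.1875/200) = (19.0%, 31.0%). So consent was given its own denominator, and fidelity was not.

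**2. Correct the denominator only.**
0.60 ± 1.96 × √(0.24/25) = 0.60 ± 0.192, or (40.8%, 79.2%). The half-width grows by 19.2 − 13.6 = 5.6 points.

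**3. Add correlation within physiotherapist.** Mean caseload m = 25/k; design effect DE = 1 + (m − 1) × ICC; half-width = 1.96 × √(0.24 × DE/25). For k = 9, m = 2.78, so DE = 1.18 at ICC 0.1 and 1.53 at ICC 0.3.

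| Physiotherapists (assumed) | ICC 0.1 | ICC 0.3 |
|---|---|---|
| 3 | (34.7%, 85.3%) | (25.6%, 94.4%) |
| 6 | (38.0%, 82.0%) | (33.2%, 86.8%) |
| 9 | (39.2%, 80.8%) | (36.2%, 83.8%) |
| 12 | (39.8%, 80.2%) | (37.9%, 82.1%) |

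With nine, the half-widths are 20.8 and 23.8 points, so clustering adds 1.6 or 4.6 points to the 19.2. Uneven caseloads raise this. With an assumed coefficient of variation of 0.7, DE = 1 + ((1 + 0.49) × 2.78 − 1) × ICC, and the half-widths become 22.0 and 26.8 points.

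**4. Compare the two sources.** Halving n doubles the variance. For clustering to do the same, DE must equal 2, so ICC = 1/(m − 1): 0.56 with nine physiotherapists, 0.32 with six, 0.14 with three. With nine, the denominator is the larger problem at any ICC below 0.56.

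**The case against.** The strongest reply is that the clustering part rests on figures the article does not give. Nine is an interview target drawn from everyone on the delegation log who agrees, so more may deliver the package. With 15 (assumed), the half-widths are only 19.8 and 21.0 points at ICC 0.1 and 0.3. Fidelity is also not purely therapist behaviour: progression of exercise plausibly depends on patients returning, the exercise is adapted to the individual, and some topics apply only to some patients. All of this lowers the correlation. This stands, and it is why the clustering effect is given as a modest, assumption-dependent range.

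It can also be said that the interval is a planning illustration, that the funder fixed the sample size, and that the analysis is descriptive. That is true, and no design choice changes. But the article itself states this precision for a stop/go outcome, and the denominator error follows from its own figures.

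A reader might go further and infer that one or two physiotherapists could settle the fidelity rating without anyone noticing. The documents do not support that. Two of nine with equal caseloads carry 2/9 = 22% of patients, but caseloads are not stated and the Table 2 cut-offs cannot be read in the text supplied, so an effect on the rating cannot be shown. Nor would it go unnoticed: fidelity is scored from each patient's case report form, added treatments are to be discussed, and delivering physiotherapists from different sites are interviewed, with the findings used to refine the package. The narrower point that remains is that the pooled percentage alone does not show the pattern.

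**Conclusion.** Wrong as written, as to stated precision. The interval of (46%, 74%) belongs to 50 independent patients. For the outcome as defined it is at best about (41%, 79%), given full recruitment and equal arms; recruiting fewer than 50 would widen it. That part needs no outside assumption.

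Correlation within physiotherapist is a secondary effect in the same direction. It gives about (39%, 81%) at ICC 0.1 and (36%, 84%) at ICC 0.3 if nine deliver the package with equal caseloads. It is large only with very few physiotherapists or a high correlation. It would be wrong to present clustering as the main reason that the interval is too narrow.

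**What to change.** 1. Restate the planning interval on about 25 intervention patients, (41%, 79%). Beside it, give the range under a stated intra-therapist correlation and the expected number of delivering physiotherapists.
2. For the final result, apply a simple design effect based on the caseloads actually seen, or show a sensitivity range over plausible correlations. Do not rely on a correlation estimated by a beta-binomial model: about nine clusters of under three patients would estimate it very imprecisely.
3. Use one interval method throughout. The choice matters at this size: with nine physiotherapists and ICC 0.3 (effective n = 25/1.53 = 16.3), Wald gives (36%, 84%) and Wilson about (37%, 80%).
4. Show fidelity by coded physiotherapist and by site beside the pooled percentage, as description only, so that a general shortfall can be told from a local one when the rating is interpreted. Confirm that the case report form, which is not shown, records a coded treating physiotherapist; add the field only if it does not.

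The cost is some wording, one small table and at most one form field. The stated precision becomes less favourable. Sample size and trial conduct are unaffected.
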